#### Drop-out criteria

Participants will be withdrawn from the trial if they meet the following criteria: (1) occurrence of any severe adverse events; (2) voluntary withdrawal from the trial; (3) not following the study protocol (i.e., drug compliance below 80%); (4) use of additional medication to improve cognitive function during the trial; (5) considered unsuitable by the principal investigator; (6) loss of ability to communicate and express their opinions.

### Enrollment

We plan to recruit a total of 84 amnestic MCI patients through physician referrals and newspaper advertisements. Candidates with memory complaints will be screened using the eligibility criteria, and the screening tools including the Korean Dementia *Screening* Questionnaire (KDSQ) and K-MMSE. SNSB will be conducted for potentially eligible participants, and those who are diagnosed with amnestic MCI will be enrolled. A clinical research coordinator and investigators will provide the participants with a detailed explanation of the study procedures, potential benefits and risks of participation. Informed consent will be obtained from all participants prior to enrollment.

### Allocation and blinding

An independent statistician will generate a random sequence using R Software version 4.1.3. All individuals will be randomly assigned to either KGT or placebo group, in a ratio of 1:1 using a block randomization with a block size of four. The random sequence will be sent to the pharmaceutical company as an encoded file, which will label and package the investigational drugs. Participants will be sequentially assigned and provided with the drug according to the randomization code in the order of enrollment. The participants, clinical psychologists, neuroimaging specialists, a clinical pharmacist, clinical research coordinator (CRC), clinical research associates (CRA), project manager (PM) of contract research organization (CRO), and study investigators will be blinded to treatment allocation until the completion of the study. Only if serious adverse events (SAEs) occur, the cases will be unblinded and the participants will be taken off trial.

### Intervention

The participants assigned to intervention group will take KGT granules (3 g /1pack) and those assigned to control group will take placebo granules (3 g /1pack). KGT is an herbal formula composed of 15 medicinal herbs. The amount and composition of each compound are presented in Table 2. *Dimocarpus Longan*, one of the herbal drugs of KGT, is a subtropical and tropical fruit of the Sapindaceae family. *D. longan* used in this trial was cultivated for medicinal purposes, not harvested from the wild. It is imported for medicinal use, and standardized, regulated, and quality controlled by the Korean Ministry of Food and Drug Safety (KMFDS) guidelines such as Korean Pharmacopoeia (KP) and Korean Herbal Pharmacopoeia (KHP). KGT will be manufactured by Han Poong Pharmaceutical Co., Ltd. (Jeonju, Korea), certified for Good Manufacturing Practices (GMP). Placebo drugs will be produced by the same manufacturer using the standard method of placebo manufacturing according to the Korean GMP guidelines. Their taste, color, shape, smell, and package will be made similar to KGT granules.

**Table 2 Tab2:** Composition of Kami Guibi-tang

Scientific name	Latin name	Amount (g)
*Panax ginseng C.A. Meyer*	Ginseng Radix	1
*Atractylodes macrocephala Koidzumi*	Atractylodis Rhizoma Alba	1
*Poria cocos Wolf*	Poria Sclerotium	1
*Astragalus membranaceus Bunge*	Astragali Radix	1
*Dimocarpus longan Loureiro*	Longanae Arillus	1
*Zizyphus jujuba Miller var. spinosa Hu ex H.F. Chou*	Zizyphi Semen	1
*Bupleurum falcatum Linné*	Bupleuri Radix	1
*Angelica gigas Nakai*	Angelicae Gigantis Radix	0.67
*Polygala tenuifolia Willdenow*	Polygalae Radix	0.67
*Gardenia jasminoides Ellis*	Gardeniae Fructus	0.67
*Paeonia suffruticosa Andrews*	Moutan Cortex	0.67
*Zizyphus jujuba Miller var. inermis Rehder*	Zizyphi Fructus	0.67
*Aucklandia lappa Decne.*	Aucklandiae Radix	0.33
*Glycyrrhiza uralensis Fischer*	Glycyrrhizae Radix et Rhizoma	0.33
*Zingiber officinale Roscoe*	Zingiberis Rhizoma Recens	0.33

An independent clinical pharmacist will distribute the granules to participants in each group. Participants will be instructed to dissolve the granules in a glass of warm water and take the solution 30 minutes before or between meals, thrice daily. The investigators and CRC will make weekly reminder phone calls to the participants during the intervention period, in order to help them adhere to medication schedule. Participants will be allowed to take drugs for underlying medical conditions during the study period; however, they will not be allowed to take any medicine that may affect cognitive function. They will be required to report all the drugs taken during the study period. The name and dosage of the medication will be recorded in the case report form (CRF). Participants will be asked to return the leftover drugs at each study visit, and the number of returned drugs will be counted for assessing drug compliance. Those who take less than 80% of study medication will be withdrawn from the study.

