### Outcome

The primary outcome includes changes in cognitive performance after the administration of KGT or placebo granules. SNSB, which is composed of various cognitive tests such as CDR, GDS, and MMSE will be conducted to assess the cognitive function, and changes in SNSB results will be analyzed. The secondary outcomes include the rate of progression to AD at the endpoint, according to NINCDS-ADRDA and CDR-GS score ≥ 1. In addition, we will measure neuroimaging signals and blood-based biomarkers. Structural MRI and functional MRI (fMRI) will be adopted to observe neuroimaging signal changes. The changes in gray matter volume will be measured using structural MRI. Also, Rs-fMRI and task-based fMRI will be performed to compare the changes in functional connectivity among working memory and default mode networks and to measure the changes in brain activation during the face–name association task and one-back working memory task. Levels of plasma Aβ42 and Aβ40 will be measured as blood-based biomarkers. The safety outcomes include electrocardiogram (ECG) and blood chemistry (Na, K, Cl, AST, ALT, BUN, Cr, glucose, LDH, CPK).

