### Adverse events (AEs)

Adverse events will be monitored at each visit, and by telephone, weekly during the intervention and biweekly for 12 weeks after the intervention. All AEs will be assessed for causality and severity, and the details of each AE will be recorded in CRF. If a serious adverse event (SAE) occurs, the participation will be terminated, and the institutional review board (IRB) will be reported as soon as possible. All AEs will be monitored until they stabilize.

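### The withdrawal rules end outcome follow-up as well as treatment, so primary-outcome data and some progression data are lost after events that decline or treatment may cause

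*Protocol article*

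**What the plan says.** Four sections of the Protocol article remove people from the trial, not only from study drug.

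- **Drop-out criteria:** "Participants will be withdrawn from the trial if they meet the following criteria: (1) occurrence of any severe adverse events". The same list includes compliance below 80%, "use of additional medication to improve cognitive function during the trial", and "loss of ability to communicate and express their opinions".
- **Intervention:** "Those who take less than 80% of study medication will be withdrawn from the study".
- **Allocation and blinding:** participants with a serious adverse event are unblinded and taken off trial.
- **Adverse events (AEs):** "If a serious adverse event (SAE) occurs, the participation will be terminated". The only observation said to continue is that of the adverse events themselves, until they stabilise.

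On measurement, the K-MMSE and SNSB section places the SNSB at baseline, week 24 and week 36, with only the K-MMSE at week 12. The Outcome section adds: "The secondary outcomes include the rate of progression to AD at the endpoint". Under Data analyses, the mITT set needs at least one examination after the start of the intervention, missing data are filled by LOCF, and a per-protocol set is defined separately.

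**The concern.** The withdrawal triggers occur after randomisation, and decline or treatment could bring them about. A participant who is getting worse may be started on a cognitive drug or may become unable to communicate. Tolerability or a perceived lack of benefit may lower compliance. Once any of these ends participation, the score that would show what happened is never collected.

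Two outcomes are exposed. The first is the change in SNSB-D, on which the trial is sized and which is meant to give confirmatory evidence. The second is progression to AD, where few events are expected and each one counts. Outcomes that were never collected cannot be recovered by a later analysis.

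Removal for low compliance also serves no analytic purpose, because the per-protocol set already exists to describe compliant participants.

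**Working it through.** **Inputs from the article.** Pilot changes in SNSB-D of +22.47 (KGT) and +8.36 (placebo); d = 0.70; two-sided alpha 0.05; power 0.80; 33 per arm evaluable; 20% dropout; 42 per arm recruited (Sample size calculation). Progression from aMCI to AD of 10–15% per year (Background).

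**1. The plan's own figure.** Normal approximation: n = 2 × (1.960 + 0.842)² / 0.70² = 32.04, rounded up to 33 per arm. The t-based power at 33 per arm is 79.97%. Dropout: 33 / 0.80 = 41.25, rounded up to 42 per arm, 84 in total. The figures reproduce. They also show that dropouts are treated as lost to analysis. The implied SD is (22.47 − 8.36) / 0.70 = 14.11 / 0.70 = 20.16.

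**2. What happens to a removed participant.**

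| Removed | SNSB available | Under LOCF |
|---|---|---|
| Before week 24 | Baseline only | Change of 0, or left out |
| Between weeks 24 and 36 | Baseline and week 24 | Week-24 value used at week 36 |

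**3. Illustration with baseline carried forward.** Assumptions: all withdrawals come before week 24; the splits are invented; those withdrawn would otherwise have changed by their arm's mean. With fraction w withdrawn, the arm mean becomes m = (1 − w) × μ and the variance (1 − w)(20.16² + μ²) − m². Power is for a t-test with 42 per arm.

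| Withdrawn KGT / placebo | Difference | d | Power |
|---|---|---|---|
| 0% / 0% | 14.11 | 0.70 | 88.7% |
| 20% / 20% | 17.98 − 6.69 = 11.29 | 0.59 | about 76% |
| 30% / 10% | 15.73 − 7.52 = 8.20 | 0.42 | about 48% |
| 10% / 30% | 20.22 − 5.85 = 14.37 | 0.76 | about 93% |

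With no drug effect and both arms at +8.36, a 30%/10% split gives (0.90 − 0.70) × 8.36 = 1.7 points, against the arm that loses more.

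**4. Illustration with removed participants left out.** Suppose there is no drug effect and those withdrawn are k SD worse than completers. The bias is then (difference in withdrawal fractions) × k × SD: 0.20 × 0.5 × 20.16 = 2.0 points, or 0.20 × 1.0 × 20.16 = 4.0 points. This time it favours the arm that loses more. Steps 3 and 4 point in opposite directions, so the sign depends on facts the article does not give.

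**5. Progression.** Expected cases per arm = 42 × [1 − (1 − a)^(weeks/52)].

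| Yearly rate a | Week 24 | Week 36 |
|---|---|---|
| 10% | 42 × 4.75% = 2.0 | 42 × 7.03% = 3.0 |
| 15% | 42 × 7.23% = 3.0 | 42 × 10.64% = 4.5 |

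If one progressor per arm were lost (an assumption), that would be 1/3.0 to 1/2.0 of the expected week-24 cases, or 1/4.5 to 1/3.0 of those expected by week 36.

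**The case against.** **Not every progressor is lost.** A reader might infer that progressors to AD as a class fall out of the progression endpoint. The article does not support that. Progression is not a withdrawal criterion, and AD first found at the scheduled week-24 assessment is recorded. Only those who first start a cognitive drug, lose the ability to communicate or meet another criterion are missed, and the article gives no rate for these routes.

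**LOCF does not always flatter.** Before week 24 the carried value is baseline. Both pilot arms improved on average, so baseline lies below the average later score. It hides a loss only for individuals who decline.

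**The mITT set does not simply become per-protocol.** Someone seen at week 12 for the K-MMSE or blood tests can meet its definition and stay in with LOCF. The defect is missing outcome data, not necessarily exclusion from the set.

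**A larger bias is not established.** A null bias near 3 points needs both arms to change by the average of the two pilot changes: 0.20 × 15.4 = 3.1. The document's placebo change gives 1.7. Differential loss is itself an inference; the pilot reported 3 dropouts among 33, high adherence and no severe adverse events.

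**Timing and fuller documents.** The article does not say whether 80% compliance is judged at each visit or cumulatively. If it is judged at the end of treatment, the week-24 SNSB may already be done. Table 1 is not shown, and an article may leave early-termination visits to the full protocol.

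The first four objections stand and limit the claim. The last stands in part: compliance timing is open, but a full protocol that kept these participants in SNSB follow-up would contradict four sections that say participation ends.

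**Conclusion.** The point holds in a limited form. As written, the rules end outcome follow-up together with treatment, so a participant removed before week 24 contributes no post-baseline primary outcome, and some progressors can leave before their progression is recorded. The comparison is then made on selected data.

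Neither the size nor the direction of the bias can be found from the article. Under the assumed splits with baseline carried forward, the effect ranges from a spurious 1.7 points when the drug does nothing to a fall from 14.11 to 8.20 when the pilot effect is real; with 10% KGT and 30% placebo withdrawn, the difference rises slightly to 14.37. Those figures show sensitivity and do not predict the result. Because 20% dropout is already in the sample size, the issue is bias more than power. For progression, 2.0 to 3.0 expected cases per arm by week 24 and 3.0 to 4.5 by week 36 leave little room to lose any.

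The sections also differ in wording: the Drop-out criteria refer to *severe* adverse events, while Allocation and blinding and Adverse events refer to *serious* ones. These are different concepts and the passages must be reconciled.

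**What to change.** In Drop-out criteria, Allocation and blinding, Intervention, and Adverse events, separate stopping study drug from leaving the study. The rules on when treatment stops remain the sponsor's; no change to them is proposed here. Then:

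- Have every participant who has not withdrawn consent and can be assessed complete the week-24 and week-36 SNSB/CDR and AD assessment, whether or not still on study drug.
- Record the reason for and date of stopping, and any cognitive drug started.
- Include these data in the efficacy analysis as randomised.
- Use the 80% compliance rule only to define the per-protocol set.
- Reconcile *severe* with *serious* across the sections.

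**Cost.** A protocol amendment while recruitment is under way, and a few extra attendances at visits that are already scheduled. Off-treatment data may dilute the estimated effect. Against that, if all 42 per arm were observed, power at d = 0.70 would be about 88.7% rather than 80.0% with 33 per arm, provided stopping treatment does not dilute the effect.

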### Outcome

The primary outcome includes changes in cognitive performance after the administration of KGT or placebo granules. SNSB, which is composed of various cognitive tests such as CDR, GDS, and MMSE will be conducted to assess the cognitive function, and changes in SNSB results will be analyzed. The secondary outcomes include the rate of progression to AD at the endpoint, according to NINCDS-ADRDA and CDR-GS score ≥ 1. In addition, we will measure neuroimaging signals and blood-based biomarkers. Structural MRI and functional MRI (fMRI) will be adopted to observe neuroimaging signal changes. The changes in gray matter volume will be measured using structural MRI. Also, Rs-fMRI and task-based fMRI will be performed to compare the changes in functional connectivity among working memory and default mode networks and to measure the changes in brain activation during the face–name association task and one-back working memory task. Levels of plasma Aβ42 and Aβ40 will be measured as blood-based biomarkers. The safety outcomes include electrocardiogram (ECG) and blood chemistry (Na, K, Cl, AST, ALT, BUN, Cr, glucose, LDH, CPK).

### Assessment

#### K-MMSE and SNSB

K-MMSE will be performed at the screening visit and at 12th week for evaluating the general cognitive status. It is one of the most widely used screening tests to estimate the cognitive functioning [12]. SNSB-II will be conducted at baseline, 24th week, and 36th week, to measure the effect of KGT on cognitive function. Changes in the mean SNSB scores will be analyzed as a primary outcome. SNSB is a neuropsychological test battery most commonly used in South Korea to estimate global cognitive function. The test is composed of various cognitive subtests that assess five domains: memory, attention, language, visuospatial function, and executive function. It also includes other related tests including CDR, K-MMSE, Korean-Instrumental Activities of Daily Living (K-IADL), Barthel-Activities of Daily Living (BADL), and Short-form Geriatric Depression Scale (SGDS) [13]. We will use a modified version of SNSB for dementia (SNSB-D), to obtain a global cognitive function (GCF) score, which is the sum of all the test scores of five domains. The maximum GCF score is 300 points: 150/300 (50%) for memory, 17/300 (6%) for attention, 27/300 (9%) for language, 36/300 (12%) for visuospatial function, and 70/300 (23%) for frontal/executive function [14]. The detailed contents of SNSB-D are presented in Table 3.

**Table 3 Tab3:** Contents of Seoul Neuropsychological Battery for dementia (SNSB-D)

Domains (total score)	Subtests	Maximum points
Attention (17)	Digit span forward	9
	Digit span backward	8
Language & related function (27)	K-BNT	15
	Calculation	12
Visuospatial function (36)	RCFT copy	36
Memory (150)	Orientation	6
	SVLT free/delayed recall	48
	SVLT recognition	12
	RCFT free/delayed recall	72
	RCFT recognition	12
Frontal/Executive function (70)	Motor impersistence	3
	Contrasting program	3
	Go-no-go test	3
	Fist-edge-palm	3
	Luria loop	3
	Categoric word generation	20
	Phonemic word generation	15
	Stroop test-color reading	20
GCF score		300

*K-BNT* Korean short version of the Boston Naming Test, *RCFT* Rey Complex Figure Test, *SVLT* Seoul Verbal Learning Test, *GCF* Global cognitive function

#### MRI

Brain MRI scans will be conducted at baseline and 24th week using a 3.0 T MRI system (Philips Ingenia, Best, The Netherlands) to observe the neurophysiological changes. During the resting acquisition, participants will be asked to be in a supine position, with their head positioned in the 32-channel head coil, fixed by soft foam pads to minimize the head movement, and to remain awake with their eyes closed. Task-based fMRI data will be obtained while participants perform a face–name association task and one-back working memory task. Blood oxygenation level-dependent (BOLD) data will be acquired using a T2-weighted gradient echo, echo-planar imaging (EPI) sequence with the following acquisition parameters: repetition time (T_R_) = 2000 ms; echo time (T_E_) = 30 ms; flip angle (FA) = 70°; field of view (FOV) = 210 × 210 × 96 mm, matrix = 70 × 70; number of slices = 32; slice thickness = 3 mm; slice gap = 0 mm; multi-band factor = 2; SENSE factor = 2; voxels = 3 × 3 × 4 mm^3^. A sagittal structural 3D T1-weighted (3D T1W) image will be acquired before and after contrast injection with a turbo fast field echo sequence, similar to the magnetization-prepared rapid acquisition of the gradient echo (MPRAGE) sequence with the following acquisition parameters: repetition time (T_R_) = 8.1 ms, echo time (T_E_) = 3.7 ms, flip angle (FA) = 8°, field-of-view (FOV) = 236 × 236 mm^2^, and voxel size = 1 × 1 × 1 mm^3.^

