#### Exclusion criteria

Participants who meet any of the following criteria will be excluded: (1) diagnosed with AD according to the criteria of the National Institute of Neurological and Communicative Disorders and Stroke-Alzheimer’s Disease and Related Disorders Association (NINCDS-ADRDA); (2) diagnosed with vascular dementia according to the criteria of the National Institute of Neurological Disorders and Stroke-Association Internationale pour la Recherche et l’Enseignement en Neurosciences (NINDS-AIREN); (3) with brain disorders that cause neurologic symptoms, other than cognitive impairment; (4) with other neurodegenerative disorders (e.g., Huntington’s disease, Parkinson’s disease, Creutzfeldt-Jakob disease and Down’s syndrome); (5) cognitive decline due to other diseases (e.g., vitamin deficiency, brain tumor, head trauma, encephalitis, hypoxic brain damage, neurosyphilis); (6) with history of major depressive disorder; (7) with psychiatric disorders or behavioral problems requiring antipsychotic medication; (8) with history of convulsive disorder, except for febrile convulsions during childhood; (9) with life-threatening or unstable medical conditions; (10) uncontrolled hypertension; (11) with heart or renal diseases; (12) with edema; (13) gastrointestinal symptoms (e.g., diarrhea, nausea, anorexia, abdominal pain); (14) use of medication that may induce myopathy or hypokalemia; (15) with hypersensitivity to ingredients in study medication; (16) abnormal range of liver and kidney function (serum aspartate aminotransferase/alanine aminotransferase (AST/ALT) levels more than two-fold the upper reference limit, or serum creatinine (Cr) levels more than 10% of the upper reference limit); (17) participating in other clinical trials within 4 weeks; (18) with illiteracy; (19) those who are contraindicated for Brain MRI; (20) any other possible conditions considered inappropriate to participate in the trial.

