#### Safety assessment

ECG and blood tests will be conducted to examine the safety outcomes. ECG will be conducted at baseline and 24th week. Blood levels of Na, K, Cl, AST, ALT, BUN, Cr, glucose, LDH, CPK will be measured at baseline, 12th, and 24th week. Vital signs will be checked at each visit. We will closely monitor any abnormal findings in vital signs, blood tests, and ECG.

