### Statistics

#### Sample size calculation

The primary outcome of interest in this study is the change in the total SNSB-D score between baseline and post-intervention. The calculation of sample size is based on a superiority test, as the aim of this study is to show that KGT is superior to placebo. Our pilot study of aMCI patients treated with KGT showed that the change in the total SNSB-D score was + 22.47, compared to + 8.36 in the placebo group. The calculated effect size (Cohen’s d) was 0.70. Using G*Power software with a power of 0.80 and a two-sided type I error of 0.05, the calculated total sample size for the current study involves 66 participants, with 33 in each group. The dropout rate was 10% (3 of 33 participants) in the previous study; however, since the current study will take a longer follow-up period, we expect the dropout rate to be 20%. We plan to recruit a total of 84 participants for this RCT (42 participants in each group).

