Next, we will perform multimodal MRI scans in this study, including structural MRI and resting-state and task-evoked functional MRIs. Structural MRI scan of brain atrophy are the most widely accepted markers of AD progression [19]. A decline in hippocampal volume has consistently been related to memory loss in the AD continuum [20]. Since fMRI, which is an indirect measure of brain activity, is useful in the detecting early alterations in brain function, it might be valuable for evaluating the physiological changes over a short time interval [21]. We will investigate the effects of KGT on brain function using both task-based and task-free (resting-state) approaches. Rs-fMRI studies have shown that the progression of memory decline in aMCI is associated with a decline in functional connectivity in DMN regions, which include brain regions related to cognitive function, such as the hippocampus and medial frontal lobe [22]. For task-based fMRI, we will adopt two types of memory paradigms: the face–name association task and the one-back working memory task. By employing cognitive tasks, the fMRI measure will provide information on the changes in brain activity while performing specific activities that mimic the actual difficulties occurring in daily life [21]. Various neuroimaging modalities will be helpful for evaluating the neural underpinning of the effect of KGT.

We will also observe changes in blood-based neuropathological biomarkers, including the plasma levels of Aβ42, which are proposed to reflect the AD pathology and associated neurodegeneration [15–17]. Plasma Aβ levels are correlated with the cerebrospinal fluid (CSF) Aβ levels and Aβ deposition in the brain [23]. Low plasma Aβ42/40 ratios are associated with an increased risk of dementia [24] and greater cognitive decline [25]. We will investigate whether KGT shows any disease-modifying effect via the plasma Aβ42/40 ratio, instead of using CSF biomarkers, which is a costly and invasive process. In addition, plasma Aβ protein levels may provide information about the etiology of MCI.

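### Contrast injection appears to be repeated at week 24, where no stated outcome, safety check or analysis names a post-contrast image; make that scan pre-contrast by default and name the T1 used for gray matter volume

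*Protocol article*

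**What the plan says.** The MRI section sets two imaging visits: "Brain MRI scans will be conducted at baseline and 24th week using a" 3.0 T scanner. It then lists the acquisition parameters once. For the structural scan it says "A sagittal structural 3D T1-weighted (3D T1W) image will be acquired before and after contrast injection with a turbo fast field echo sequence". No visit is singled out, and no reason for the contrast is given.

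The uses of imaging are stated elsewhere in the article:

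- Outcome: "The changes in gray matter volume will be measured using structural MRI". The other imaging outcomes are resting-state connectivity and task activation.
- Discussion: structural imaging is justified by atrophy and hippocampal volume ("Structural MRI scan of brain atrophy are the most widely accepted markers of AD progression").
- Outcome: one secondary endpoint is "the rate of progression to AD at the endpoint, according to NINCDS-ADRDA", together with a CDR global score of at least 1.
- Safety assessment: "ECG and blood tests will be conducted to examine the safety outcomes", with vital signs at each visit.

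**The concern.** Contrast injection is the one invasive element of the imaging, and participants are 55 to 90 years old. A trial procedure of this kind should serve a stated purpose at each visit where it is done. At baseline a purpose is easy to supply: the exclusion criteria cover other brain disorders and cognitive decline from causes such as "brain tumor, head trauma, encephalitis, hypoxic brain damage, neurosyphilis", and a contrast scan could help exclude some of these. By week 24 eligibility is settled, and the article names no use for the second post-contrast image.

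A smaller point follows from the same sentence. Two T1 images are acquired per visit, and the article does not say which one supplies gray matter volume.

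What is at stake is avoidable exposure and scan time. Both arms have the same scans, so the comparison between them is not affected.

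**Working it through.** **1. Is contrast planned at week 24?** The MRI section names both visits in its first sentence and gives a single parameter list, with the T1 before and after contrast. Read literally, this applies to both visits. That is an inference, because Table 1 could show a difference between visits and is not shown.

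**2. Does any stated week-24 use name a post-contrast image?**

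| Possible use | Section | What is stated |
|---|---|---|
| Purpose of the scans | MRI | Neurophysiological change; no diagnostic or safety purpose |
| Gray matter volume | Outcome; Discussion | Structural MRI; pre- or post-contrast not specified |
| Connectivity, task activation | Outcome; MRI | BOLD data; contrast not mentioned |
| Progression to AD | Outcome | NINCDS-ADRDA and CDR global score; no imaging criterion stated, criteria not reproduced |
| Safety | Safety assessment; Adverse events | ECG, blood tests, vital signs, adverse events; no MRI read |
| Analysis | Data analyses | fMRI measures named; no enhancement measure |
| Eligibility | Exclusion criteria | Applies at entry, not at week 24 |

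None does. The progression row is the only one left open. A pre-contrast T1 with the same sequence is acquired in any case, so gray matter volume can be measured without contrast.

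**3. How many injections?** The input is the planned sample of 84 (Sample size calculation). That figure reproduces: with d = 0.70, two-sided alpha 0.05 and power 0.80, the normal approximation gives 2 × (1.960 + 0.842)² / 0.70² = 32.04, rounded up to 33 per arm, 66 in total. The t-test solution is 33.02 per arm, with power 0.7997 at 33. Allowing for 20% dropout, 33 / 0.80 = 41.25, rounded up to 42 per arm, 84 in total.

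Week-24 injections = 84 × (1 − dropout before week 24):

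- No dropout: 84.
- Pilot dropout ("The dropout rate was 10% (3 of 33 participants) in the previous study", which is 9.1%): 84 × 30/33 = 76.4, about 76.
- Expected dropout of 20%: 84 × 0.80 = 67.2, about 67.

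The last two counts assume that all dropout occurs before the week-24 scan. Later dropout moves them toward 84. Over both visits the literal reading gives up to 2 × 84 = 168 injections, or 84 + 67 = 151 at 20% dropout, against at most 84 if contrast is confined to baseline.

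**4. How many could still be spared?** Recruitment began on 4 February 2022 (Trial status). If the first baseline scan fell on that day, the first week-24 scan would be 168 days later, on 22 July 2022. The article appeared on 2 December 2022 and the trial runs to May 2025, so some week-24 scans may predate any amendment. The documents do not give the number.

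**The case against.** The strongest reply is that this argues from silence. A journal article condenses the protocol. The MRI section reads as a list of scanner settings, and the imaging manual or Table 1 may limit contrast to baseline or give its purpose. This stands in part: it makes repetition at week 24 an inference and lowers confidence. It does not remove the point, because the article does more than leave something out. It fixes an invasive procedure in a sentence that covers both visits.

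The second reply concerns diagnosis. Progression to AD is judged after baseline, and Data analyses compares conversion to normal cognition or dementia between groups. A reader might infer from the table above that a week-24 contrast scan has no possible use. The documents do not support that: the NINCDS-ADRDA criteria are not reproduced, so a role in attributing a new decline to AD or to another cause cannot be excluded. That would justify contrast in the individuals concerned; the article gives no reason for routine use in everyone.

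The third reply is that a reader might assume gray matter volume already comes from the pre-contrast T1, so that nothing in the outcome would change. The article says only structural MRI. If the pipeline uses the post-contrast image, dropping it at week 24 without further instruction would break the comparison with baseline. This reply stands, and the fix has to deal with it.

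Finally, the exclusions for renal disease, raised creatinine and contraindication to MRI already lower the risk. They do so, but they supply no reason to inject.

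**Conclusion.** The point holds in a limited form. On the natural reading contrast is repeated at week 24, and no outcome, safety check or analysis stated in the article names a post-contrast image there. Making that scan pre-contrast by default would spare up to 84 injections, about 67 at 20% dropout, less those already given.

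This rests on two assumptions: that the single acquisition description applies to both visits, and that gray matter volume can be taken from the pre-contrast T1 at both. The article gives no harm rate, so no harm is quantified. Sample size, power, type I error, blinding and the primary outcome are unaffected.

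A reader might extend the criticism to baseline contrast. The documents do not support that, because exclusion of brain lesions is a plausible use at entry. Low severity, low-to-medium confidence.

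**What to change.** In the MRI section and the scanning procedure:

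- Make the week-24 structural scan pre-contrast only by default. Contrast may stay at baseline if it serves lesion exclusion.
- Allow contrast at week 24 only where clinically indicated for an individual, for example to attribute a new decline.
- State that gray matter volume is taken from the pre-contrast T1 at both visits. If analysis has started from the post-contrast image, reprocess the stored pre-contrast images so that every participant has the same source.
- If contrast was never planned at week 24, correct the sentence to say so.

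The cost is a short mid-trial amendment and the loss of a week-24 post-contrast image that no listed endpoint uses. Participants already scanned at week 24 would hold one extra image, which does no harm once the pre-contrast T1 is fixed as the source. Contrast and scan time are saved at each later week-24 visit.
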